## Abstract

**Background:**

The increase in the number of cancer cases and the evolution of cancer care management have become a significant problem for the French health care system, thereby making patient empowerment as a long sought-after goal in chronic pathologies. The implementation of an activation measure via the Patient Activation Measure-13 item (PAM-13) in the course of cancer care can potentially highlight the patient’s needs, with nursing care adapting accordingly.

**Objective:**

The objectives of this PARACT (PARAmedical Interventions on Patient ACTivation) multicentric study were as follows: (1) evaluate the implementation of PAM-13 in oncology nursing practices in 5 comprehensive cancer centers, (2) identify the obstacles and facilitators to the implementation of PAM-13, and (3) produce recommendations for the dissemination of such interventions in other comprehensive cancer centers.

**Methods:**

This study will follow the “Reach, Effectiveness, Adoption, Implementation, and Maintenance” framework and will consist of 3 stages. First, a robust preimplementation analysis will be conducted using the Theoretical Domains Framework (TDF) linked to the “Capability, Opportunity, Motivation, and Behavior” model to identify the obstacles and facilitators to implementing new nursing practices in each context. Then, using the Behavior Change Wheel, we will personalize a strategy for implementing the PAM-13, depending on the specificities of each context, to encourage acceptability by the nursing staff involved in the project. This analysis will be performed via a qualitative study through semistructured interviews. Second, the patient will be included in the study for 12 months, during which the patient care pathway will be studied, particularly to collect all relevant contacts of oncology nurses and other health professionals involved in the pathway. The axes of nursing care will also be collected. The primary goal is to implement PAM-13. Secondary factors to be measured are the patient’s anxiety level, quality of life, and health literacy level. The oncology nurses will be responsible for completing the questionnaires when the patient is at the hospital for his/her intravenous chemotherapy/immunotherapy treatment. The questionnaires will be completed thrice in a year: (1) at the time of the patient’s enrollment, (2) at 6 months, and (3) at 12 months. Third, a postimplementation analysis will be performed through semistructured interviews using the TDF to investigate the implementation problems at each site.

**Conclusions:**

This study would improve the implemented targeted nursing interventions in cancer centers so that a patient is offered a personalized cancer care pathway. Furthermore, measuring the level of activation and the implementation of measures intended to increase such activation could constitute a significant advantage in reducing social health inequalities.

**Trial Registration:**

ClinicalTrials.gov NCT03240341; https://clinicaltrials.gov/ct2/show/NCT03240341

**International Registered Report Identifier (IRRID):**

DERR1-10.2196/17485

## Introduction

### Background

The increase in the number of cancer cases and the evolution of cancer care management have been generating a shift toward chronicity since many years. This phenomenon poses a significant problem for the French health care system [1,2]. As the number of patients treated as outpatients increases, the duration of hospitalization decreases and the care pathways become more complex [1,3,4]. The first 2 French cancer plans have given a structure to the field of cancer care in the domains of both treatment and research [5,6]. The objective of the 2014-2019 French cancer plan was to improve the interfaces between the different fields of interventions for a smoother transfer of innovation and for more fluidity in cancer care pathways [1]. However, the French health care system is centered on acute care whether it involves the management of benign acute diseases combining simple technical procedures or a multitude of complex interventions to treat the severity of acute diseases [7]. One can therefore comprehend the difficulty of integrating chronic care into hospitals in terms of its organization and due to certain attitudes adopted by caregivers. Three types of interventions were identified as part of the research conducted within our health services and performance research team, the objective of which is the performance of the provision of care and the performance of the patient pathway: (1) intervention to improve patient navigation (patient navigation) [8], (2) intervention to support and improve health literacy [9,10], and (3) intervention to support and improve patient empowerment during care (patient empowerment) [11]. These 3 types of interventions are considered to be evidence-based since they have been assessed in an experiential or quasi-experiential context to optimize the care pathway.

### Types of Interventions

#### Patient Navigation

According to the patient navigation experience developed by Harold Freeman in 1990 in Harlem for breast cancer screening, the aim of “Nurse Navigation” in the United States or “Pivot Nurses” in Canada is to better guide patients through a complex care pathway [12,13]. The principle of navigation serves to eliminate barriers having an adverse effect on the quality of care in all phases of prevention, detection, treatment, and posttreatment [14-17]. In France, patient navigation was implemented in oncology clinics with the national initiative of cancer coordination nurses in accordance with the 2009-2013 French Cancer Plan [17]. However, not all French hospitals employed navigation nurses.

#### Health Literacy

The term “health literacy” is based on the definition given by Sørensen, since it is an accepted reference at the European level [18]. She defines health literacy as “the knowledge, skills, motivation, and ability of an individual to identify, understand, evaluate, and use health information when making decisions in the health care, disease prevention, and health promotion contexts to maintain or improve the quality of life” [18]. It has been established that doctors often communicate ineffectively with their patients by providing them with explanations that are theoretically beyond their comprehension, leading to a relatively low health literacy. The most affected areas include the general context, explanations of the patient’s state of health, and treatment methods [19]. Research has objectively demonstrated that when doctors provide their patients with useful health information while also responding to patients’ emotions, the latter express a greater sense of control and hope, which has a direct positive impact on their quality of life as well as on their chances of survival [20]. It therefore seems evident that clear communication adapted to the patient is essential in the management of care for patients with cancer. After all, patients must assimilate a sum of complex explanations in order to make informed decisions about their treatment options and management of their symptoms [21]. Specifically, in oncology clinics, being mindful of patients’ needs in terms of health literacy is an important aspect of treatment since it results in care that is both focused and safe [22]. Furthermore, various studies indicate that a low level of health literacy can have an impact on the following parameters [23,24]: (1) readmission and recourse to hospitalization, (2) problems understanding medical prescriptions, (3) increase in adverse effects, (4) less awareness regarding prevention, (5) higher prevalence of health risk factors, (6) low autonomy in chronic disease management, (7) poor health outcomes, (8) less effective communication with health care professionals, (9) increased health care costs, and (10) poor general health and increased mortality.

The REALM-R (rapid estimate of adult literacy in medicine-revised) is a health literacy test that was developed to evaluate patients in a clinical setting [25]. Bass et al provided evidence to support the validity and reliability of a shortened version of the REALM [26]. Grandjacquot recently adapted it in the French language and the test proved effective in detecting inadequate levels of health literacy [27].

#### Patient Empowerment

This process was developed in the United States of America and Canada with the concept of activation and has not yet been widely applied in France. It is defined as a process of knowledge acquisition, skill development, and self-esteem development, thereby enabling the patient to be an actor or to engage in a proactive manner for his or her health care [28,29]. The Patient Activation Measure (PAM) was developed by Hibbard et al ﻿to assess knowledge, skills, and confidence in managing health [30,31]. This questionnaire can be used at different times of care [31,32]. The PAM-13 item (PAM-13) is the shortened version of the PAM. It is actually used in several contexts of disease and in many countries around the world [31,33-39]. In particular, Prey et al have demonstrated its reliability and validity while using it with inpatient individuals in oncology clinics [40]. The PAM-13 is used to determine the patient’s score and activation level [41]. Four activation levels are defined: “believes active role important” (level 1), “confidence and knowledge to take action” (level 2), “taking action” (level 3), and “staying the course under stress” (level 4). A validated French version is available (Multimedia Appendix 1).

In general, the lower the level, the more passive the patients behave in regard to their health; the higher the level, as measured by the PAM-13, the more proactive patients are with regard to their health. In all probability, the latter group would commit to improving their health behaviors [38,42]. The importance of the patient’s role in self-management of chronic illness, including making daily decisions about treatment, physical activity, or diet, has been increasingly recognized [43,44]. A high activation level can result in improved health-friendly behaviors [45], appropriate use of the health care system [42,46], a critical perspective and participation in decision-making processes with stakeholders in the health care system [42], improved management [47] and better control of chronic diseases [48,49], and a reduction in health care costs [50]. Patients with a high activation level generally manifest less misguided practices of care and better treatment adherence [46,51]. This concept of commitment can be initiated and applied to treatment and to the management of services and establishments or health policies [52].

### Objective of This Study

We believe that effective action in cancer care requires progressive patient empowerment. Several studies have illustrated the role doctors play in the patient activation process [53-56]. However, nearly all such studies have focused on basic care, with the general practitioner positioned as the “gatekeeper.” Hospitals and their staff can contribute to improving health-related behaviors and mobilizing their patients [57,58]. Nevertheless, in comprehensive cancer centers, the modulation of activation is likely varied and more complex because these facilities differ in terms of the specificities of nursing specialties they offer. Nursing positions and the provision of supportive care in oncology clinics can vary greatly depending on the hospital; for example, there are nurse navigators, nurse educators, dieticians, oncopsychologists, osteopaths, physiotherapists, hypnotherapists, and nurses specialized in tobacco cessation. We can suppose that the patients’ activation is therefore largely modulated by the type of nurse and supportive care implemented within the hospital. Therefore, we can also assume that these varying cancer care pathways also lead to different results when considering vulnerabilities, access to specific measures, quality of life, and, consequently, patient activation. The World Health Organization has stated that although certain patients will be able to mobilize their own resources and succeed in coping with the situation, thereby eventually becoming (pro)active, others will need to be guided by their caregivers [59]. The implementation of an activation measure via the PAM-13 by navigation nurses or other registered nurses would highlight the patients’ needs [60].

We are aware of the need to perform a periodic screening to identify new patient needs that emerge over time and adapt nursing measures to these needs that arise in the course of the cancer care pathway [61,62]. In addition, van Houtum et al suggest that patient activation is not a stable parameter in patients with chronic disease [63]. Greene et al provide a longitudinal measurement of PAM in order to better understand the timing of the activation process [41]. In France, the first results of the Observatory on Patient Expectations of the Unicancer Group, and more recently, findings of the new 2014-2019 Cancer Plan III (Objectives 2 and 7), underlined the need to shift current practices of care toward a more holistic view of the patient with cancer [1].

The PARACT (PARAmedical Interventions on Patient ACTivation) multicentric study aims to (1) evaluate the implementation of PAM-13 in oncology nursing practices in 5 comprehensive cancer centers, (2) identify the obstacles and facilitators to the implementation of PAM-13 at the different sites, and (3) produce recommendations for the dissemination of the intervention in other comprehensive cancer centers.

## Methods

### Implementation Study

This is an implementation multicentric study. The PARACT study is part of the realistic evaluation of an intervention as described by Pawson and Tilley following Campbell’s work [64]. This approach favors multisite and multidisciplinary assessments to study the interactions of context-mechanism-outcomes configurations. This type of evaluation makes it possible to adapt the interventions according to the results observed, while considering the context. The assessment selected for this study will therefore be multidisciplinary, combining public health teams and human and social sciences teams. The aspect of navigation in establishments will be assessed in accordance with current recommendations [65]. The patient will act as his/her own control. Given that we are conducting a study of an implementation that is complex, the study will follow the RE-AIM (Reach, Effectiveness, Adoption, Implementation, and Maintenance) framework. The implementation process will consist of 3 stages (Figure 1).

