#### Step 2: Implementation of the PAM-13 and Patient Enrollment

##### Number of Subjects Needed

As this is an implementation study, it is not possible to calculate a sample size required to respond to an efficacy hypothesis. The goal is to observe how many patients will be involved in the measurement of PAM-13 in real life. It is therefore not possible at this juncture to determine a set number of patients to be reached before ending the study.

Nevertheless, in order to stay within the confines of the study budget, it seems reasonable to limit the number of enrollments to approximately 150 patients per center in order to have a sufficient understanding of the implementation of the PAM-13 in the different facilities. A total of up to 600 patients will be included in the 5-site study (up to 150 patients per site). Two establishments will include a maximum of 75 patients per site.

We will implement the PAM-13 at each center and the study may begin enrolling patients, as outlined below.

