##### Screening and Inclusion

The oncologists, and, as a priority, the cancer nurse navigator (if the establishment employs one) or an oncology care nurse involved in the announcement of the diagnosis, and finally, a registered nurse at the choice of the investigator of the different investigative centers will suggest patients who meet the inclusion criteria to participate in the PARACT study. First, the procedure and aim of the study will be explained to the patient, and then, he or she will be given a consent form to sign. Patients will have a period of reflection of at least half an hour—seemingly sufficient—considering the extremely low risk factor of participating in the PARACT study. The patients’ inclusion must be completed within 15 days of the consultation to announce the cancer pathology. The patient will be included in the study for a period of 12 months. During his or her involvement, the patient care pathway will be studied, particularly to collect all relevant contacts of oncology nurses and other health professionals involved in the cancer care pathway. Axes of nursing care will also be collected. The primary goal is PAM-13. Secondary factors to be measured are the patient’s level of anxiety according to the HAD scale, the assessment of patients’ quality of life as measured by the EQ-5D-3L questionnaire, and the level of health literacy by using the REALM-R screening instrument. The oncology nurses in charge of treating the patient in the cancer care pathway will be responsible for completing each of the questionnaires when the patient is at the hospital for his/her intravenous chemotherapy or immunotherapy treatment. The questionnaires will be completed 3 times in the course of 1 year: (1) at the time of the patient’s enrollment in the study, (2) at 6 months, and (3) at 12 months.

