Initially, univariate analysis with chi-squared tests (or Fisher exact if the conditions are not met) for qualitative variables and Student two-sided *t* test (or Wilcoxon test if the conditions are not met) for quantitative variables will be performed.Subsequently, multivariate analysis with all exploratory variables with a significance threshold lower than 0.2 will be introduced into the multivariate model. The interactions between the variables will be ensured in advance. If an interaction is detected, the choice of the variable to be introduced will be made based on clinical relevance. The choice of the best multivariate model will be made using a selective downward procedure on the Akaike information criteria.Health literacy will be assessed via the score obtained by the REALM-R (a score <6 demonstrating a low health literacy score). The before/after health literacy increase will be assessed using a McNemar chi-square test using the score qualitatively (threshold at 6). A logistic regression model with random effect will be used in the multivariate analysis to eliminate any confounding factors with the same methodology as described above. The same methodology will be applied to the HAD scale (threshold at 11). The analysis of quantitative scales such as the EQ-5D-3L or the confidence level will be performed with matched (or otherwise Wilcoxon) Student tests between inclusion and M12. Random multivariate linear models will be implemented to adjust for any confounding variables. For the EQ-5D-3L, analyses of time until deterioration can be implemented if necessary.

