Finally, we assume that studying the implementation of a tool for measuring the degree of activation of the patient of nursing practices in oncology would enable a dynamic evaluation of changes in the patient’s cancer care pathway in order to optimize the latter. The implementation methodology using the RE-AIM evaluation framework would specify the real-life efficiency of the PAM-13, the different adaptations of the centers that have implemented it routinely, the key success factors and pitfalls to avoid, and the various parameters impacting its efficiency [66]. Due to the study and its resulting detailed and analytical description of the contents of the use of the PAM-13 in the comprehensive cancer center concerned, we will produce recommendations for the dissemination of such an intervention in order to manage the deployment of an activation measurement for all new patients with cancer at any requesting facility.

In conclusion, this study of implementation conducted at 5 French comprehensive cancer centers could help define a new strategy for sustaining patients’ empowerment in the cancer care pathway. The use of a PAM would constitute a notable change in the management of patients with cancer. Systematic integration of the measure should make it possible to implement targeted oncology nursing interventions, strengthening some of them in order to offer patients a personalized cancer care pathway adapted to their needs. Indeed, with the arrival of immunotherapy combinations, it appears essential to focus on patients’ empowerment in the management of their medical care. Moreover, the measurement of the level of activation and the implementation of measures to strengthen such activation would constitute a significant advantage in reducing social health inequalities.

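### The own-control statement does not hold: no change over time without PAM-13 is observed, so before/after changes cannot show the effectiveness of PAM-13

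*Protocol article*

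**What the plan says.** All references are to the Protocol article.

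- **Control.** Implementation Study: "The patient will act as his/her own control". No other control group or control period is described.
- **Order of events.** Number of Subjects Needed: "We will implement the PAM-13 at each center and the study may begin enrolling patients". The preimplementation stage (Step 1) consists of interviews with nurses and collects no patient scores.
- **Timing of scores.** Screening and Inclusion sets three assessments: enrolment, 6 months and 12 months. On the first: "The patients’ inclusion must be completed within 15 days of the consultation to announce the cancer pathology".
- **Stability of the outcome.** Objective of This Study cites earlier work said to "suggest that patient activation is not a stable parameter in patients with chronic disease".
- **Analyses.** Statistical Analysis, Design: "The before/after health literacy increase will be assessed using a McNemar chi-square test", with the same method for the HAD scale. EQ-5D-3L and the confidence level get paired t or Wilcoxon tests between inclusion and month 12. For PAM-13, the mean 12-month change at the nurse-navigator center is compared with that at each of the other four, and a mixed linear model describes its course. The threshold is 5% and missing values are not imputed.
- **Conclusions announced.** Implementation Study lists the intervention's effectiveness as one of four RE-AIM elements to be measured. The Discussion says the RE-AIM evaluation "would specify the real-life efficiency of the PAM-13".

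**The concern.** A patient serves as his or her own control for an intervention effect when the same patient's course is also seen without the intervention, or when that course can safely be taken as flat. Neither applies here. All follow-up takes place under PAM-13, and the article itself cites evidence that activation does not stay constant. The first score also falls close to the cancer announcement, at the start of a year of treatment, so there are plausible reasons for scores to move whatever PAM-13 does.

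At stake is what the study may conclude. A significant 12-month change, favorable or not, could be put down to PAM-13 and carried into the recommendations for dissemination, although the data cannot show its cause.

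**Working it through.** **Step 1. The article's own figure.** The enrolment cap is 600 over five sites, with three sites at up to 150 and two at up to 75: 3 × 150 + 2 × 75 = 600. It reproduces. It is a budget limit; no power, effect size or standard deviation is stated, so there is no power figure to check.

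**Step 2. What a within-patient change contains.** Write the expected inclusion-to-12-month change at center *c* as

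E[change] = drift_c + δ_c,

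where δ_c is the effect of PAM-13 with any care adapted to it, and drift_c is everything else: disease course, treatment, adaptation after the announcement and usual nursing care. Identifying δ_c requires drift_c to be known or observed in unexposed patients or periods. The article describes no pre-implementation patient cohort, run-in, staggered start or non-implementing center. In addition, without imputation the pairs come from patients still assessed at 12 months, so selective dropout can shift the observed mean change further.

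**Step 3. Does the comparison between centers supply the missing part?**

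E[change_navigator] − E[change_other] = (drift_nav − drift_other) + (δ_nav − δ_other).

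All five centers use PAM-13. If its effect is the same everywhere, δ cancels exactly. In a simulation of the t test on change (150 against 150, 2,000 runs), the rejection rate was 5.9% both with a common PAM-13 effect of 0 and with one of 5 SD. The contrast therefore carries no information on a common effect. If the effect differs by center, the contrast mixes that difference with the difference in drift.

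**Step 4. Does the modeling help?** A time effect in the PAM-13 mixed model estimates drift + δ. Adjusting for patient characteristics, as planned for the other scales, does not create an unexposed course to subtract.

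**Step 5. Illustration of size.** The article gives no drift, SD of change or completion rate; every such value here is an assumption. Set δ = 0 and let the natural drift be *d* SDs of the change score. For a two-sided 5% paired test on *n* pairs (normal approximation):

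P(significant) = Φ(d√n − 1.96) + Φ(−d√n − 1.96).

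Example: n = 600, d = 0.1 gives d√n = 2.449, and Φ(0.489) + Φ(−4.409) = 0.688.

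| Drift *d* (assumed) | n = 600 (cap, no dropout) | n = 300 (assumed completers) |
|---|---|---|
| 0 | 5% | 5% |
| 0.05 | 23% | 14% |
| 0.1 | 69% | 41% |
| 0.2 | 99.8% | 93% |

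For McNemar with discordant proportions p₁ and p₂, let D = p₁ − p₂ and S = p₁ + p₂. Then SE₀ = √(S/n), SE₁ = √((S − D²)/n), and

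P = Φ((D − 1.96 SE₀)/SE₁) + Φ((−D − 1.96 SE₀)/SE₁).

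| p₁ against p₂ (assumed) | n = 600 | n = 300 |
|---|---|---|
| 12% against 8% | 59% | 34% |
| 15% against 8% | 95% | 72% |

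Drift may go in either direction, so a significant result could equally be a deterioration. The paired figures bear on EQ-5D-3L and the confidence level, and the McNemar figures on REALM-R and HAD, the scales for which those tests are named.

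**The case against.** The best defense is that the own-control sentence may only mean an ordinary within-patient before/after comparison. The study is also framed as implementation research and realistic evaluation, its three aims contain no efficacy aim, and the sample-size section says it cannot be sized for an efficacy hypothesis. The efficiency sentence is conditional Discussion wording and is credited to the RE-AIM evaluation as a whole, not to the before/after tests.

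Much of this is fair, and it rules out several stronger readings that a reader might infer:

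- **That there is no baseline.** The enrolment score presumably precedes any care adapted to it, so it is a valid pre-response baseline. What is missing is an unexposed change over time.
- **That PAM-13 itself gets a pooled paired test which drift would make significant.** The article names paired tests for other scales. Its stated PAM-13 comparison is between centers, where drift common to all centers cancels. Only a time effect in the mixed model would share the problem.
- **That the effectiveness element would be declared positive almost regardless.** The main text does not say how that element is scored, the appendix with the RE-AIM outcomes is not at hand, and drift could be unfavorable or negligible.
- **That the Discussion's sentence on the impact of nursing makes the same claim.** It concerns nursing care by type of facility, with PAM-13 as the measuring instrument.

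What the defense does not remove is the statement of a control that the design lacks, beside two statements that promise effectiveness or efficiency. The efficacy disclaimer concerns sample size and withdraws neither.

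**Conclusion.** The point holds and should be corrected. As written, the article claims a design property it does not have, and announces a conclusion about PAM-13 that neither the before/after comparisons nor the contrast between centers can support. This follows from the order of implementation and enrolment, the three assessment times and the use of PAM-13 at all five centers; it depends on no assumed number.

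The numerical size is illustrative only. With zero PAM-13 effect and 600 pairs, the chance of a significant paired result runs from 5% with no drift to 23%, 69% and 99.8% at 0.05, 0.1 and 0.2 SD. These figures rest on assumed drift and complete follow-up at the cap.

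The scope is limited. Reach, adoption, maintenance, and the aims on obstacles, facilitators and recommendations need no control and are unaffected.

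**What to change.** Four changes of wording in the Protocol article:

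1. **Implementation Study:** replace the own-control sentence with a statement that the study makes an uncontrolled within-patient before/after comparison.
2. **Statistical Analysis, Design:** state that inclusion-to-12-month changes in PAM-13, REALM-R, HAD, EQ-5D-3L and confidence are reported as estimates with 95% CIs and are not attributed to PAM-13.
3. **Implementation Study, list of RE-AIM elements:** describe the E element as change observed during implementation.
4. **Discussion, sentence on efficiency:** make the same replacement.

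Leave the Discussion's sentence on the impact of nursing intervention by type of facility, and the three aims, as they are.

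No patients, visits or data are added. The cost is a more modest effectiveness claim. If the investigators want to keep that claim, they would need unexposed patient data, for example a pre-implementation cohort or a staggered start by center, which is a far larger change.
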